# Vitamin D and omega-3 fatty acid supplements in children with autism spectrum disorder: a study protocol for a factorial randomised, double-blind, placebo-controlled trial

**DOI:** 10.1186/s13063-016-1428-8

**Published:** 2016-06-23

**Keywords:** Autism, ASD, Vitamin D, Omega-3 fatty acids, Supplements

## Abstract

**Background:**

There is strong mechanistic evidence to suggest that vitamin D and omega-3 long chain polyunsaturated fatty acids (n-3 LCPUFAs), specifically docosahexaenoic acid (DHA), have the potential to significantly improve the symptoms of autism spectrum disorder (ASD). However, there are no trials that have measured the effect of both vitamin D and n-3 LCPUFA supplementation on autism severity symptoms. The objective of this 2 × 2 factorial trial is to investigate the effect of vitamin D, n-3 LCPUFAs or a combination of both on core symptoms of ASD.

**Methods/design:**

Children with ASD living in New Zealand (*n* = 168 children) will be randomised to one of four treatments daily: vitamin D (2000 IU), n-3 LCPUFAs (722 mg DHA), vitamin D (2000 IU) + n-3 LCPUFAs (722 mg DHA) or placebo for 12 months. All researchers, participants and their caregivers will be blinded until the data analysis is completed, and randomisation of the active/placebo capsules and allocation will be fully concealed from all mentioned parties. The primary outcome measures are the change in social-communicative functioning, sensory processing issues and problem behaviours between baseline and 12 months. A secondary outcome measure is the effect on gastrointestinal symptoms. Baseline data will be used to assess and correct basic nutritional deficiencies prior to treatment allocation. For safety measures, serum 25-hydroxyvitamin D 25(OH)D and calcium will be monitored at baseline, 6 and 12 months, and weekly compliance and gastrointestinal symptom diaries will be completed by caregivers throughout the study period.

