### Aims

To establish the vitamin D and RBC fatty acid status of children with ASD living in Auckland, New ZealandTo investigate the effect of improving either vitamin D or omega-3 status in reducing the symptoms of ASD including sociocommunicative functioning, sensory issues and aberrant behaviours (primary outcomes) and gastrointestinal symptoms (secondary outcome)To establish the effectiveness of supplementation with combined vitamin D and n-3 LCPUFAs in reducing the symptoms of ASD including sociocommunicative functioning, sensory issues and aberrant behaviours (primary outcomes) and gastrointestinal symptoms (secondary outcome)

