### Participants

This study is a collaboration between Massey University and the Waitemata District Health Board (WDHB), New Zealand. Caregivers of children who meet the criteria for the study will be approached in the first instance by the WDHB Developmental Coordinators.

We calculated that 42 participants (a minimum of 34 participants, and allowing for a 20-% potential dropout rate) would be required for each arm of the trial to demonstrate a clinically significant difference at 80 % power and 5 % statistical significance. Power calculations were based on a 17-unit difference between supplemented groups and placebo in change from baseline to endpoint on the Social Responsiveness Scale (SRS) total score [62], on a mean SRS and standard deviation of 105 and 24.7 units in untreated children with ASD, respectively (from our 2015 pilot study, unpublished). The sample size was calculated using the formula below [63]:$$ N= 2{\alpha}^2K/{\left({\mu}_2\hbox{-} {\mu}_1\right)}^2 $$

where *N* is the sample size required per group, *α* is the SD, K is the constant (7.9 denotes 80 % power and 5 % significance), and (*μ*_2 −_*μ*_1_) is the difference in SRS total score between groups.

To ensure that the study is adequately powered, a blinded interim analysis at >50 % of the initially planned enrolment will be performed by an independent third party to estimate the variance for potential sample size increase.

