Baseline characteristics of participants will be compared among groups using analysis of variance (ANOVA) for parametric data and the Kruskal-Wallis test for non-parametric data. The primary analysis, comparing the effects of treatment on symptoms of autism over 12 months, will be conducted using a generalised linear mixed-models procedure. Treatments and time will be included as fixed effects and the interactions between interventions and time will be tested. If significant main effects or interaction effects are observed, post-hoc analysis with Bonferroni adjustments will be performed. Potential confounding factors and effect modifiers (e.g. baseline 25(OH)D and RBC fatty acids, symptoms of autism at baseline, age and gender) will be investigated within the model. Logistic regression will be used to test the multiplicative interaction. Rothman’s synergy index, which would be equal to unity under additivity, and less than unity when suggesting antagonism, will be utilised to examine the postulated interaction effect of vitamin D and omega-3 LCPUFAs on core symptoms of ASD.

The secondary analysis, comparing the effects of treatment on gastrointestinal symptoms over 12 months, will be conducted using the same procedure. Potential confounding factors and effect modifiers (e.g. baseline diagnosis of any gastrointestinal symptoms and medication/supplement use) will be investigated within the model.

Differences between participants who complete and withdraw from the trial will be analysed using an independent *t* test or the Mann–Whitney test for continuous variables (e.g. age) and chi-square for categorical variables (e.g. gender).

Associations between severity of ASD symptoms and nutritional status (specifically, vitamin D, RBC fatty acids, iron and vitamin B_12_) at baseline will be assessed using regression analysis. The information will be used to assess treatment response according to tertiles of nutritional status showing significant relationship with severity of ASD.

Both intention-to-treat and per-protocol analyses will be utilised, though the primary method of analysis will be intention-to-treat. Statistical significance will be based on two-tailed tests with *P* <0.05 considered significant.

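### Three unranked primary scales, each at two-sided 5 %, in a trial sized on one of them: if any one suffices, the false-positive chance is about 1.6 to 2.9 times the stated level

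*Protocol article*

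**What the plan says.** The abstract sets three primary outcomes: "The primary outcome measures are the change in social-communicative functioning, sensory processing issues and problem behaviours between baseline and 12 months". The Aims, the caption of Fig. 1, Table 1 and Table 2 repeat the same three. Table 1 gives the instruments as SRS-2, SPM and ABC-C, all completed by the caregiver. No place ranks them.

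Under Data handling and statistical analysis, one sentence sets the level for all tests: "Statistical significance will be based on two-tailed tests with *P* <0.05 considered significant". The same section has the article's only multiplicity rule: once a main or interaction effect is significant, the follow-up comparisons are Bonferroni-adjusted. The rule is not stated to extend across the three scales.

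The sample size, under Participants, uses one scale: "Power calculations were based on a 17-unit difference between supplemented groups and placebo in change from baseline to endpoint on the Social Responsiveness Scale" (total score). The spread is taken from pilot data, "on a mean SRS and standard deviation of 105 and 24.7 units in untreated children with ASD". The calculation uses 80 % power and a single 5 % level.

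**The concern.** The 5 % in the sample-size calculation belongs to one test on one scale, while the outcome list offers three scales on which a primary result could be declared. The Hypotheses speak of the severity of ASD symptoms in general, so a significant result on any one scale could be put forward as confirming them. The Bonferroni step applies only after a significant effect, so it does not protect the tests that open the way to it.

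At stake is the error rate behind the headline claim. The abstract's Discussion says that showing efficacy of either supplement or both would reveal a non-invasive approach to managing symptoms. A reader would take that claim to carry a 5 % false-positive risk, and under an any-one-scale reading it carries more.

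**Working it through.** **1. The plan's own figure.** Inputs from Participants: SD 24.7, difference 17, K = 7.9.

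N = 2 × SD² × K / difference² = 2 × 24.7² × 7.9 / 17² = 33.35, so 34 per arm. With 20 % dropout, 33.35 / 0.8 = 41.7, so 42 per arm, and 4 × 42 = 168. (Starting from the rounded 34 gives 42.5, so 43; the difference is immaterial.) Power at 34 per arm is 81 % by the normal approximation and 79.9 % by the t test. The stated size is reproduced for one comparison, on one scale, at one 5 % level.

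**2. Three scales, one treatment effect, any one sufficing.** With independent scales: 1 − 0.95³ = 0.143, and 0.143 / 0.05 = 2.9 times.

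The article gives no correlations between the scales, so a common correlation ρ is assumed and varied. Results come from 200,000 simulated null trials with four equal arms of 34, each effect tested at two-sided 5 %; the ρ = 0 entry is the exact value.

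| ρ | At least one false positive | Multiple of 5 % |
|---|---|---|
| 0 | 14.3 % | 2.9 |
| 0.5 | 12.5 % | 2.5 |
| 0.7 | 11.0 % | 2.2 |
| 0.8 | 9.8 % | 2.0 |
| 0.9 | 8.4 % | 1.7 |

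**3. Crediting the Bonferroni step.** Here treatment is one four-level factor. Each scale has an overall test at 5 %, followed by six pairwise comparisons at 0.05 / 6, and a claim counts only if a pair is significant.

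| ρ | At least one false positive | Multiple of 5 % |
|---|---|---|
| 0 | 10.9 % | 2.2 |
| 0.5 | 9.8 % | 2.0 |
| 0.8 | 7.9 % | 1.6 |

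Across steps 2 and 3, for correlations from 0 to 0.8, the range is 1.6 to 2.9 times.

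**4. A separate layer: several treatment effects per scale.** If vitamin D, omega-3 and their interaction were each tested unadjusted on each scale, there would be nine tests: 1 − 0.95⁹ = 0.370 if independent, about 33 % at ρ = 0.5 and about 27 % at ρ = 0.8. Two supplement effects on three scales give 1 − 0.95⁶ = 0.265 if independent.

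**5. Cost of the two remedies.**
- *SRS-2 as the single primary outcome.* The calculation in step 1 applies as it stands: 168 children.
- *Splitting alpha equally over three scales (0.05 / 3 = 0.0167).* The same normal-approximation calculation gives 45 evaluable per arm; 45 / 0.8 = 56.25, so 57 per arm, and 4 × 57 = 228. Keeping 34 evaluable per arm would lower power on SRS total to 67 % (normal approximation) or 65 % (t test).

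**The case against.** The strongest reply is that the any-one-scale rule is inferred. No sentence says that one significant scale is enough, and the Aims join the three outcomes with *and*. If all three had to be significant there would be no inflation. This stands, and it makes the error figures conditional. It does not rescue the design: requiring all three would call for power on all three, and the article gives power for one.

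A second reply is that rules on multiplicity often sit in a statistical analysis plan, which is not available here, and that a journal article is condensed. That is fair for missing detail. But the article itself fixes three unranked primaries, one blanket level, the place where Bonferroni applies and the single outcome that sized the trial. These stated choices do not fit together.

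A third reply is that the scales are unlikely to be independent. The same caregiver completes all three and their content overlaps: SRS-2 and ABC both cover stereotypic behaviour, and all three touch on social engagement. This stands, so 14.3 % is an upper bound for one effect and the values at higher correlations are more realistic.

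A reader might infer from the 2 × 2 design that the inflation reaches five to seven times 5 %. The text does not support that. The analysis section enters treatments and time as fixed effects, tests the interactions of the interventions with time, and sends the interaction of the two supplements to logistic regression and Rothman's synergy index. It nowhere specifies three unadjusted factorial tests on each scale. Even if they were done, a factor above seven needs independent scales. Whether two supplements in a factorial trial form one error family is itself contested.

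**Conclusion.** The point holds in a limited form. Three outcomes are primary without ranking, every test is at two-sided 5 %, the only adjustment comes after a significant effect, and the sample size with its 5 % level covers SRS total alone. If a positive result on any one scale supports the efficacy claim, the false-positive chance for one treatment effect is about 8 to 14 %, or 1.6 to 2.9 times the stated level.

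This rests on two assumptions: that one scale suffices, on which the article is silent, and that the correlation between scales lies between 0 and 0.8, for which it gives no figure. At 0.9 the unadjusted single-effect figure is 8.4 %. Figures up to 37 % belong to the separate question of how many treatment effects are tested per scale and should not be attributed to the three outcomes.

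This should be fixed, but it is not a fatal flaw: the outcomes are prespecified and visible, and the repair is a matter of wording.

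**What to change.** Before unblinding, amend the protocol and the registry entry to:

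- name SRS-2 total score at 12 months as the single primary outcome, at two-sided 5 %, because it is the scale that sized the trial;
- make SPM and ABC-C key secondary outcomes, tested only if SRS-2 is significant, either in a fixed stated order or by Holm.

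The planned 168 children stay unchanged. The article reports the trial as still recruiting, with allocation concealed through the data analysis, so the change can be made blind. The downside is that a benefit seen only on SPM or ABC-C could not be claimed as a primary result.

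Naming one primary outcome does not settle how many treatment effects are tested on SRS-2. If vitamin D, omega-3 and their interaction are to be tested separately, the amendment should also say which of them carries the primary claim and at what level.

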**Discussion:**

To our knowledge there are no randomised controlled trials assessing the effects of both vitamin D and DHA supplementation on core symptoms of ASD. If it is shown that either vitamin D, DHA or both are effective, the trial would reveal a non-invasive approach to managing ASD symptoms.

**Trial registration:**

Australian New Zealand Clinical Trial Registry, ACTRN12615000144516. Registered on 16 February 2015.

**Electronic supplementary material:**

The online version of this article (doi:10.1186/s13063-016-1428-8) contains supplementary material, which is available to authorized users.

## Background

Autism spectrum disorder (ASD) is a neurodevelopmental disorder usually diagnosed when developmental, educational and social demands increase [1]. ASD is believed to affect 1 % of the New Zealand population [1]. Diagnostic criteria for ASD include delays or difficulties in sociocommunicative functioning, restricted and repetitive behaviours/interests, sensory issues and aberrant behaviours [1, 2]. ASD is also associated with medical conditions such as gastrointestinal problems [1–5]. The clinical symptoms of individuals with ASD vary widely [5–7], suggesting that it is multi-factorial in nature.

It is generally agreed that both genetic and environmental factors contribute to the development of ASD. The high heritability of ASD has been shown by twin and familial studies [8, 9]. However, it has been reported that only 30 % of ASD cases are clearly associated with a syndrome or genetic markers leaving the aetiology of most cases without explanation [10].

Mechanistic evidence, as well as a scattering of ecological and cross-sectional studies, suggests that vitamin D may play an important role in the aetiology of ASD. Vitamin D receptors and 1α-hydroxylase have been identified in different regions of the brain and sensing neurons [11–13]. The active form of vitamin D has been shown to have an important role in the neuronal differentiation, structure, function and connectivity of the developing brain [14]. Vitamin D response elements have been identified on genes involved in serotonin and oxytocin synthesis [15]. Lower levels of plasma oxytocin [16] and abnormal serotonin concentrations in the brain and tissues outside the blood–brain barrier have been shown in populations with ASD [17, 18]. Oxytocin and serotonin have been implicated in modulating social behaviour [19, 20].

The serum level of 25-hydroxyvitamin D (25(OH)D), the best available marker of vitamin D status [21, 22], has been shown to be significantly lower in autistic individuals than in their healthy counterparts [23, 24]. Similarly, higher prevalence of ASD has been reported at higher latitudes and in individuals exposed to lower UVB radiation levels [24, 25]. In adults with severe autism living in a community centre in Italy, problem behaviours significantly increased during spring and decreased during autumn [26]. Depletion of vitamin D in body stores by the end of winter and early spring seasons (due to lack of sun exposure) may have exacerbated the symptoms of autism and increased problem behaviours observed in this study.

The potential role of vitamin D deficiency in autism has received surprisingly little attention. While a few case studies have reported beneficial effects of vitamin D supplementation on autistic core symptoms [27], no randomised, placebo-controlled trial with vitamin D supplementation has been conducted to date [28]. Jia et al. [27] reported that shifting serum 25(OH)D concentration in a child with ASD from 31 to 203 nmol/L after 2 months of high-dose vitamin D supplementation (150,000 international units (IU) per month administered intramuscularly plus 400 IU per day administered orally) improved autistic core symptoms. Although other trials investigating the effect of multivitamin/mineral supplements containing low doses of vitamin D on autism symptoms have provided promising results [29, 30], the individual effect of each nutrient cannot be determined from these studies.

Omega-3 long chain polyunsaturated fatty acids (n-3 LCPUFAs) also have the potential to positively affect children with ASD. These n-3 LCPUFAs, mainly DHA, are necessary for normal development and functioning of the brain and auditory and visual processing system [31–33]. Long-term DHA depletion results in significant losses in brain DHA with consequent loss of brain function [34]. Evidence shows that children with ASD have an increased omega-6 to omega-3 ratio in blood and low blood concentrations of n-3 LCPUFAs, which could be due to either low dietary intake or differences in fatty acid metabolism and incorporation into cellular membranes of children with ASD [35–37].

Reports on the benefits of n-3 LCPUFAs in treating ASD are inconclusive. There are, to our knowledge, only four randomised, placebo-controlled trials [38–41], three of which are small pilot studies. Bent et al. [40] and Amminger et al. [39] found that omega-3 supplementation was superior over a placebo (12 and 6 weeks, respectively) for reducing symptoms of hyperactivity and stereotypic behaviour in children with ASD. However, more recent studies have found that supplementation with n-3 LCPUFAs for 6 months had no beneficial effect on core symptom domains of ASD in children aged 2 to 5 years (*n* = 38) [41] and 3 to 10 years (*n* = 48) [38]. However, these studies are limited by their low participant numbers and short treatment periods.

In addition to these studies on the nutrients’ effects when given individually, there are speculations that vitamin D and n-3 LCPUFAs may improve ASD symptoms because of their shared functions and each nutrient-specific role that complements the other nutrient’s functions [42, 43]. Both nutrients are powerful anti-inflammatory agents, immune modulators and neuroprotectors [42]. Furthermore, evidence suggests that while vitamin D regulates serotonin synthesis, omega-3 fatty acids increase serotonin release and membrane fluidity and thus increase serotonin accessibility [43]. ASD is associated with increased inflammation, oxidative stress, immune dysregulation and/or mitochondrial dysfunction in brain regions that are involved in social behaviour, sensory and motor coordination, memory, speech and auditory processing, and also with neurotransmitter dysregulation [17, 18, 44].

Gastrointestinal problems have also been reported to be common in children with ASD. Compared to their typically developing siblings (12 %), autistic children have more gastrointestinal symptoms (42 %) [3–5]. Gastrointestinal problems may relate to abnormal gut flora [45], decreased activity of digestive enzymes [46] or increased intestinal permeability [47]. Vitamin D deficiency has been implicated in the pathophysiology of some gastrointestinal diseases, including inflammatory bowel disease [48], and thus might play a role in ASD-related gastrointestinal problems. Likewise, n-3 LCPUFAs have been shown to reduce symptoms of ulcerative colitis [49], to support epithelial integrity in vitro [50], and to alter the gut microbiota composition of both neurodevelopmentally normal and early life-stressed animals [51].

Unusual eating habits, a risk factor for nutrient deficiencies, are common in ASD [4]. Inadequate intakes of magnesium, zinc, folate, vitamins A, E, B_12_, K and D, as well as low intake of foods rich in n-3 LCPUFAs, have been reported in children with autism [52–58]. However, a broad picture of the nutritional status of affected children in New Zealand is lacking.

### Hypotheses

Both vitamin D and omega-3 status, defined as omega-3 index (red blood cell (RBC) DHA + eicosapentaenoic acid (EPA)), will be low in children with ASD at baseline (25(OH)D <75 nmol/L [59] and omega-3 index of approximately 4–6 % [60, 61])Improving either vitamin D or omega-3 status with supplementation will reduce the severity of ASD symptoms in children with ASDCombined vitamin D and n-3 LCPUFA supplementation will be more effective than either supplement alone or placebo in reducing the severity of ASD symptoms in children with ASD

### Aims

To establish the vitamin D and RBC fatty acid status of children with ASD living in Auckland, New ZealandTo investigate the effect of improving either vitamin D or omega-3 status in reducing the symptoms of ASD including sociocommunicative functioning, sensory issues and aberrant behaviours (primary outcomes) and gastrointestinal symptoms (secondary outcome)To establish the effectiveness of supplementation with combined vitamin D and n-3 LCPUFAs in reducing the symptoms of ASD including sociocommunicative functioning, sensory issues and aberrant behaviours (primary outcomes) and gastrointestinal symptoms (secondary outcome)

## Methods/design

This study consists of two stages: stage 1 will include recruitment and screening, while stage 2 is a vitamin D and n-3 LCPUFA randomised, double-blind, placebo-controlled trial (Fig. 1). The duration of the intervention is 12 months.

**Fig. 1 Fig1:**
[figure not shown]
Schematic diagram of study design. ^1^Blood biomarkers: 25-hydroxyvitamin D (25(OH)D), red blood cell (RBC) fatty acids, calcium, albumin, iron studies, vitamin B_12_, folate, full blood count and vitamin A. Questionnaires: sociodemographics, medical history, eating/mealtime behaviours and food diary. ^2^Questionnaires: sociocommunicative functioning, sensory problems and aberrant behaviours (primary outcomes); gastrointestinal symptoms (secondary outcome), sun exposure and skin colour. Anthropometry: weight and height. ^3^Blood biomarkers: 25(OH)D, RBC fatty acids, calcium and albumin. Questionnaires: sociocommunicative functioning, sensory problems, aberrant behaviours (primary outcomes) and eating/mealtime behaviours and diet quality. Anthropometry: weight and height. ^4^Blood biomarkers: 25(OH)D, calcium and albumin. *Gastrointestinal symptoms (secondary outcome) and medication/supplement use/incidence of adverse events/supplement compliance will be monitored throughout the study period

Stage 1 will provide the opportunity for a comprehensive description of the study population with respect to nutritional status (biochemical indices and dietary intake), demographics and medical history. Stage 2 will demonstrate the efficacy of supplementation with vitamin D, n-3 LCPUFAs or both on reducing ASD symptoms.

